### **Severe adverse events**

Severe adverse events, including mortality, will be recorded on the CRF, and a dedicated SAE report form. The expectedness and possible or probable causal link to the study gas will be judged by medical officers. The SAE forms will be reported to the trial PIs within 24 hours. Of note, significant mortality (estimated 20%) is expected in this trial of critically ill children with severe malaria. Unexpected SAEs will be reported to

MUREC and the DSMB within 15 days (if not life-threatening) and within 7 days in the case of a life-threatening unexpected SAE. As an additional measure, mortality events will be graphically recorded in real time with every consecutive group of 10 enrolled patients. Statistical thresholds have been defined to trigger a safety review if mortality is above expected levels. Quarterly reports of the cumulative trial mortality by study group will be provided to the DSMB.

### ***Quality***

#### ***Intervention***

Administration of study gas will be directly supervised by dedicated trial nurses, who will record the time the patient receives the gas during each shift (8h period) on the CRF. Because patients may not tolerate a mask after partial recovery, the time on the study gas may be less than 72 hours.

#### ***Protocol deviations***

Protocol deviations will be noted on the CRF as well as a central log.

#### ***Blinding***

We will assess whether blinding has been successful by asking key trial persons (caregivers, health professionals, outcome assessors) to guess patients' treatments and compare the answers with the actual treatments[88]. These will be recorded on the CRF.

## **5 SELECTION AND WITHDRAWAL OF SUBJECTS**

### **5.1 Inclusion criteria**

1. Age 1-10 years

2. Positive malaria rapid diagnostic test in the presence of selected features of severe malaria.
3. Willing and ability to complete follow up schedules for the study – 14 day and 6 months after hospital discharge.

## **5.2 Exclusion criteria**

1. Baseline methemoglobinemia (>2%)
2. Known renal, cardiac, or hepatic disease or other chronic illnesses like diabetes, epilepsy, cerebral palsy, clinical AIDS, suspected or known hemoglobinopathy (e.g., sickle cell anemia, G6PD deficiency).
3. Suspected bacterial meningitis.
4. Patient already received parenteral quinine in the ED prior to eligibility assessment.
5. Patient unlikely to tolerate delivery mask for more than 24 hours.
6. Severe malnutrition
7. Severe malarial anemia (Hb <50g/L) without other signs of severe malaria.

---

 repeated seizures (two or more generalized seizures in 24 h); prostration (in children 1 year and older, the child is unable to sit unsupported or stand although was able to before the illness; impaired consciousness (Blantyre Coma Score <5 in children 1 to 4 years, GCS <14 for children ≥ 5 years); respiratory distress: sustained nasal flaring, deep breathing or intercostal/subcostal retractions.

### **5.3 Subject withdrawal criteria (terminating trial treatment)**

#### **(a) When and how to withdraw subjects from the trial**

We distinguish between adverse events that will result in temporary discontinuation of the study gas with the possibility of re-challenge after return to normal levels, and adverse events that will lead to patient withdrawal from the study.

#### ***Temporary discontinuation of treatment***

Treatment with study gas (iNO or placebo) will be temporarily discontinued if the following adverse events occur:

- Methemoglobinemia
- Elevated inspired NO2 concentration
- Persistent hypoxemia
- Evolving respiratory distress
- Unexplained tachycardia
- Unexplained hypotension
- Any study drug related adverse event that, in the opinion of the investigator, makes it unsafe for the subject to continue

Details and operational definitions are provided in SOP: discontinuation of study gas.

Subjects may be rechallenged with study gas (iNO or room air) after metHb, SpO2, HR, or SBP return to normal levels after discontinuation of study gas (iNO or room air).

#### ***Permanent Discontinuation of treatment***

If a subject experiences any of the following events during the 3 day iNO delivery period the study gas should be permanently discontinued:

- Refractory methemoglobinemia
- Hemoptysis
- Acute kidney injury

- Any study drug related adverse event that, in the opinion of the investigator, makes it unsafe for the subject to continue
- Any study drug related adverse event that repeats upon re-challenge at the same or lower dose level
- At the discretion of the subject or guardian
- At the discretion of the Investigator, if deemed appropriate, for any reason

Patients meeting these criteria will have study gas removed, and will be continued to be monitored until resolution of the abnormality. When study gas is permanently discontinued, patient data will continue to be collected for primary and secondary trial endpoints, including daily bloodwork. These results will be included in an *intention-to-treat* analysis.

**(b) The type and timing of data to be collected for withdrawn subjects:**

If for any reason a subject does not complete the study, the reason will be entered on the CRF. All subjects are free to withdraw from participation at any time, for any reason, specified or unspecified, and without prejudice. The reason for the early termination will be recorded. The time to resolution of the abnormal result, and any clinical sequelae must also be recorded.

Patients for whom study gas is permanently discontinued will continue to have data collected for primary and secondary trial endpoints, including daily bloodwork. Their results will be included in an intention-to-treat analysis.

**(c) Whether and how subjects are to be replaced:**

At the midway point of recruitment (90 patients enrolled), an assessment will be made of the number of patients with complete and accurate evaluable data. The current

sample size is estimated for a dropout rate of 10%. If treatment discontinuation and/or withdrawal exceeds 10%, a sample size recalculation will be considered to adjust for greater than expected loss of evaluable patients without compromising study power.

**(d) The follow-up for subjects withdrawn from trial treatment**

If a subject is withdrawn because of an adverse event, the subject will be followed and treated by the medical officer until the abnormal parameter or symptom has resolved or stabilized.

The adverse events must be followed to resolution and the follow-up evaluations noted in Adverse Event CRF and recorded when the subject has stabilized.

## **6 TREATMENT OF SUBJECTS**

### **6.1 Description of intervention**

*Product:* Gaseous nitric oxide

*Dose:* 80 ppm

*Dosing schedule:* Continuous

*Route:* Inhalation (non-rebreather HiOx® face mask)

*Treatment period:* Maximum 72 hours (may be discontinued earlier if patient recovers and no longer tolerates face mask)

Gaseous NO (delivered with air and oxygen as carrier) at a concentration of 80 parts per million (ppm) will be administered continuously by inhalation (non-rebreather HiOx®

face mask) for a maximum of 72 hours. Subjects in the control arm will receive room air as a placebo for a maximum of 3 days. The iNO dose of 80 parts per million is US-FDA approved for use in neonates (see *INOMax product monograph*).

To monitor the inspired nitric oxide, nitrogen dioxide (NO2) and oxygen concentrations, a US-FDA approved gas monitor will be used. Should the NO or NO2 concentrations fall outside the targeted range, an operator set alarm will sound. The trial manager or designee (unblinded) will be available on a 24 hour basis to respond to monitor alarms.

Nitric oxide will be delivered as long as possible with the above device, up to a maximum of 72 hours. However, as the subject improves in the course of the disease, recovers consciousness, begins ambulating, and/or no longer tolerates the mask delivery system, the study gas may be discontinued earlier than 72 hours. At this point after significant disease resolution, it is expected that the continued benefit of iNO will be negligible. The trial manager or designee (unblinded) will be responsible for initiating the study gas (iNO or room air placebo), monitoring the inhaled NO, NO2 and O2 levels as well as patient methemoglobin levels, responding to any monitor alarms, initiating corrective actions, and informing the treating physicians, if necessary. We will monitor peripheral oxyhemoglobin saturation, and use the minimum inspired O2 concentration (above 21%) required to maintain a PaO2 ≥ 92%.

As a primary safety measure, every patient will be monitored with a US-FDA approved pulse CO-oximeter for methemoglobin and arterial oxygen saturation. This will assure, metabolically, that too much nitric oxide is not being inhaled and that the inspired oxygen concentration is correct.

Each subject will receive their own mask to avoid cross contamination. During study gas treatment, a nurse will be present at all times. A physician (medical officer) will follow patients daily, and will be on call on a 24 hour basis. Nurses and physicians will be trained in the clinical recognition of methemoglobinemia and its management before commencement of the trial. Thresholds for temporary discontinuation of study gas or withdrawal from the study based on methemoglobin measurements are given in section *5.3 Subject withdrawal criteria*.

Both treatment arms (iNO and room air placebo) will receive standard antimalarial therapy and supportive measures according to Ugandan national guidelines.

## **6.2 Co-administered treatments during the trial**

All patients in the trial will receive Uganda standard of care treatment for severe malaria. This will include anti-malarial therapy (generally intravenous quinine), supportive therapy with intravenous fluids, blood transfusion, glucose, antipyretics, and anticonvulsants as needed, and treatment for suspected bacterial co-infection with broad-spectrum antibiotics at the treating physicians discretion. There is no restriction on medications/treatments for patients in the trial.

## **6.3 Procedures for monitoring subject compliance**

Patients will be directly observed in the hospital by dedicated trial nurses. The time that they remain on the study gas will be recorded each shift. In the event that the mask is

not tolerated by children in the study, this will be recorded in the nursing record (case report form).

## **7 ASSESSMENT OF EFFICACY**

### **7.1 Specification of efficacy parameters**

*Primary endpoint:* Daily rate of change of ANG-2

*Secondary endpoints:*

1. Clinical efficacy:
  - a. 48 hour and 14-day mortality
  - b. recovery times:
    - i. time to fever resolution
    - ii. time to sit unsupported
    - iii. time to hospital discharge
  - c. time to parasite clearance
  - d. incidence of recrudescence at day 14
2. Other biomarkers and genetic determinants of malaria disease severity
  - a. whole blood lactate level
  - b. biomarkers and genetic determinants of endothelial activation, inflammation and coagulopathy
3. Neurocognitive outcome at 6 months after discharge

**Primary outcome**

The daily change in Ang-2 over the hospital admission will be the primary efficacy outcome. Elevated Ang-2 levels are associated with poor clinical outcome in severe malaria[33, 34] and Ang-2 has been used to follow disease progression and recovery in previous studies of malaria[33]. Thus, Ang-2 is an objective, quantitative marker of disease severity, validated for longitudinal follow-up of patients with malaria. Ang-2 levels will be measured longitudinally at admission (day 0), day 1, day 2 and day 3 of hospital admission. In patients treated for severe malaria who survive the infection, Ang-2 levels have been shown to decrease linearly during recovery at a mean rate of 2700pg/mL per 24h[33].

**Secondary outcomes****Therapeutic efficacy**

We will examine the efficacy of adjunctive iNO treatment using established clinical and parasitological outcomes: in-hospital mortality, recovery times (time to fever resolution, time to sit unsupported, and time to hospital discharge), time to parasite clearance, incidence of parasite recrudescence at day 14 after hospital discharge. These are standard outcomes in other therapeutic trials for malaria[64, 81, 82]. Routine intensive monitoring of vital signs, clinical assessments on at least a daily basis by physicians experienced in the management of severe malaria, as well as measurement of key laboratory parameters and parasite density will be performed to collect this data.

**Biomarkers and genetic determinants of disease severity**

Lactate is produced by the anaerobic metabolism of glucose in the absence of adequate tissue oxygenation. As such, elevated lactate levels represent a final common pathway

of tissue hypoxia and decompensated shock, the forerunner of cardiovascular collapse and death. Lactate levels at presentation predict pediatric mortality in a wide variety of clinical conditions including malaria[83, 84], sepsis[85], pediatric trauma[86] and cardiac disease[87]. We will measure lactate as an independent biomarker of disease severity during the clinical trial.

Biomarkers and genetic determinants of severe malaria may provide additional insight into the pathways and processes altered in cerebral malaria and affected by iNO delivery. We plan to examine biomarkers of endothelial activation, inflammation including cytokines, and coagulopathy which are central to the pathophysiology of severe malaria. In addition, genetic pathways involved in severe malaria and response to iNO will be investigated.

### ***Neurocognitive outcome***

In order to establish whether iNO improves long-term neurocognitive outcomes in children with severe malaria, we will also establish the areas, frequency and severity of cognitive and neurologic function affected by cerebral malaria in children of different ages up to age 5. The overall cognitive deficit at 6 months after discharge will be assessed by doing neuropsychological tests as described in SOPs.

## **7.2 Methods and timing for assessing, recording, and analyzing efficacy parameters**

Clinical outcomes will be assessed daily by trial nurses and medical officers. They will be recorded on standardized case report forms. The data will be entered into a computerized database. Statistical analysis for the primary endpoint is described in

section 9.1 *Statistical methods*. In brief, a mixed-effects linear model will be used to determine differences in the change of Ang-2 over the first 72 hours of hospital admission.

## **8 ASSESSMENT OF SAFETY**

Adverse events may occur commonly in a trial involving children with severe malaria, although the majority of events are likely due to the clinical course of malaria and not to study medications. Mortality in children at nearby Mulago Hospital with severe malaria was as high as 16% among children with impaired consciousness and 21% among children with deep acidotic breathing as presenting clinical signs[80].

### **8.1 Specification of safety parameters**

The following standard definitions are based on the International Committee on Harmonization Guideline on Clinical Safety Data Management.

#### ***Adverse Event (or Adverse Experience)***

*Any untoward medical occurrence in a patient or clinical investigation subject administered a pharmaceutical product and which does not necessarily have to have a causal relationship with this treatment.*

An adverse event (AE) can therefore be any unfavourable and unintended sign (including an abnormal laboratory finding), symptom, or disease temporally associated with the use of a medicinal product, whether or not considered related to the medicinal product.

In this trial, a running log of adverse events will be kept and reviewed periodically to allow the study team to assess if any patterns in adverse events emerge in real time.

### **Adverse Drug Reaction (ADR)**

Inhaled nitric oxide has been used in clinical practice and in several clinical trials, and is a marketed medicinal product. Regarding *marketed medicinal products*, a well-accepted definition of an adverse drug reaction in the post-marketing setting is:

*A response to a drug which is noxious and unintended and which occurs at doses normally used in man for prophylaxis, diagnosis, or therapy of disease or for modification of physiological function.*

The iNO product monograph defines the following adverse reactions that occurred in at least 5% of patients receiving INOmax in the CINRGI study with event rates >5% and greater than placebo event rates[89].

Table 3. Adverse events associated with the use of iNO.

| Adverse Event | Placebo
(n=89) | Inhaled NO
(n=97) |
|----------------------|---------------------------|------------------------------|
| Hypotension          | 9 (10%)                   | 13 (13%)                     |
| Withdrawal           | 9 (10%)                   | 12 (12%)                     |
| Atelectasis          | 8 (9%)                    | 9 (9%)                       |
| Hematuria            | 5 (6%)                    | 8 (8%)                       |
| Hyperglycemia        | 6 (7%)                    | 8 (8%)                       |
| Sepsis               | 2 (2%)                    | 7 (7%)                       |
| Infection            | 3 (3%)                    | 6 (6%)                       |
| Stridor              | 3 (3%)                    | 5 (5%)                       |
| Cellulitis           | 0 (0%)                    | 5 (5%)                       |

In addition, the following adverse drug reactions have been reported during post-approval use of iNO: dose errors associated with the delivery system; headaches associated with environmental exposure of iNO in hospital staff; hypotension associated with acute withdrawal of the drug; hypoxemia associated with acute withdrawal of the drug; pulmonary edema in patients with CREST syndrome. These reactions are reported voluntarily from a population of uncertain size; therefore, it is not always possible to estimate their frequency reliably or to establish a causal relationship to drug exposure.

For the purposes of safety monitoring and reporting, adverse drug reactions will include temporary as well as permanent discontinuation of the study gas. Criteria have been established for temporary and permanent study gas discontinuation, and are listed in sections 4.6 Description of stopping rules/discontinuation criteria, and 5.3 Subject withdrawal criteria (terminating trial treatment).

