##### ***Permanent Discontinuation of treatment***

If a subject experiences any of the following events during the 3 day iNO delivery period the study gas should be permanently discontinued:

- Refractory methemoglobinemia
- Hemoptysis

- Acute kidney injury
- Any study drug related adverse event that, in the opinion of the investigator, makes it unsafe for the subject to continue
- Any study drug related adverse event that repeats upon re-challenge at the same or lower dose level
- At the discretion of the subject or guardian
- At the discretion of the Investigator, if deemed appropriate, for any reason

Patients meeting these criteria will have study gas removed, and will be continued to be monitored until resolution of the abnormality. When study gas is permanently discontinued, patient data will continue to be collected for primary and secondary trial endpoints, including daily bloodwork. These results will be included in an intention-to-treat analysis.

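### Section 8.1 counts discontinuation of study gas as an adverse drug reaction, so stops at guardian or investigator discretion enter the reaction count although they need involve no reaction

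*Protocol*

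**What the plan says.** Section 8.1 of the protocol adopts the standard post-marketing definition of an adverse drug reaction: "A response to a drug which is noxious and unintended", at doses normally used. It then adds a rule for this trial: "For the purposes of safety monitoring and reporting", "adverse drug reactions will include temporary as well as permanent discontinuation of the study gas". The next sentence says which discontinuations are meant: "Criteria have been established for temporary and permanent study gas discontinuation, and are listed in sections 4.6" and 5.3.

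The temporary criteria in 4.6 and 5.3 are introduced as adverse events. The permanent criteria are wider. Besides clinical events they include "At the discretion of the subject or guardian" and "At the discretion of the Investigator, if deemed appropriate, for any reason".

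Separately, section 6.1 provides that if the child improves or "no longer tolerates the mask delivery system, the study gas may be discontinued earlier than 72 hours". Sections 4.4 and 4.5 say much the same, and the Quality part of section 4.9 expects time on gas to fall short of 72 hours after partial recovery.

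**The concern.** A reaction is something the drug does to the patient. A discontinuation is a management action that can have many causes. Section 8.1 treats the second as an instance of the first and sets no condition on the reason. A guardian who simply withdraws the child from gas therefore produces an adverse drug reaction in the count, in either arm, including in a child breathing room air.

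Tolerability and safety of iNO form specific aim 3 in section 3. A reaction count that blends toxicity with refusal and discretion, and possibly with recovery, does not answer that aim. Nor is this a detail left to a later analysis plan, since the protocol itself fixes the rule.

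**Working it through.** **1. Reading the passages together.** The protocol states no expected reaction or discontinuation rate, so there is no figure of its own to reproduce. The check is first one of definition.

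| Reason for stopping gas | In the 4.6/5.3 lists? | Requires an adverse event? | Counted as a reaction by 8.1? |
|---|---|---|---|
| Temporary criteria (e.g. methemoglobinemia, unexplained hypotension) | Yes | Yes | Yes |
| Permanent clinical criteria (e.g. hemoptysis, acute kidney injury) | Yes | Yes | Yes |
| Guardian or subject choice | Yes | No | Yes |
| Investigator discretion | Yes | No | Yes |
| Recovery or mask intolerance (4.4, 4.5, 6.1) | Not named | No | Unclear |

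Rows three and four are certain on any reading, because 8.1 cites exactly the lists in which they stand. Row five is open. Sections 4.4, 4.5 and 6.1 use the word discontinued for these stops, section 9.5 lists intolerance as a cause of premature discontinuation of gas, and the investigator-discretion item could absorb them. But the lists that 8.1 cites do not name them.

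**2. Is there a filter elsewhere?** The paragraph on unexpected reactions in 8.1 requires judged relatedness, but only for unexpected reactions. Section 4.9 records the date, time and reason for each stop, and possible or probable causality for adverse events. Section 8.1 uses neither to decide what counts.

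**3. Size, as an illustration.** All rates here are assumed. Let g be the true reaction rate in an arm and s the share of children with a stop unrelated to any reaction, independent of g. The apparent rate is 1 − (1 − g)(1 − s). With n = 90 per arm (section 9.2) and two-sided alpha 0.05, power is Φ[(d − 1.96·se0)/se1], where d is the difference in apparent rates, se0 = √[2·p̄(1 − p̄)/90] with p̄ the mean of the two rates, and se1 = √{[p1(1 − p1) + p2(1 − p2)]/90}.

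*Dilution, with the same s in both arms and a true 5% versus 15%:*

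| s in both arms | Apparent rates | Difference | Ratio | Power |
|---|---|---|---|---|
| 0 | 5% v 15% | 10 points | 3.0 | 61% |
| 10% | 14.5% v 23.5% | 9 points | 1.62 | 34% |
| 20% | 24% v 32% | 8 points | 1.33 | 22% |
| 40% | 43% v 49% | 6 points | 1.14 | 12% |

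First row: se0 = √(2 × 0.10 × 0.90/90) = 0.0447 and se1 = √(0.175/90) = 0.0441, so (0.10 − 0.0877)/0.0441 = 0.28 and Φ(0.28) = 0.61. Fourth row: 1 − 0.95 × 0.60 = 0.43 and 1 − 0.85 × 0.60 = 0.49; se0 = 0.0743 and se1 = 0.0742, so (0.06 − 0.1456)/0.0742 = −1.15 and Φ(−1.15) = 0.12.

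*Equal true rates of 5%:* with s = 20% in both arms the apparent rates are 24% v 24%, which is inflation without a false difference. Only unequal s creates one. If s is 20% on placebo and 30% on iNO, the rates are 24.0% v 33.5% (29% chance of a significant excess). If s is 20% v 40%, they are 24.0% v 43.0% (78%).

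*Unequal recovery stops alone:* 36 v 49 children of 90 gives p̄ = 85/180 = 0.472, standard error 0.0744 and z = (13/90)/0.0744 = 1.94, just short of 1.96. With 36 v 45, z = 1.35.

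**The case against.** The strongest reply is that 8.1 is less open than it looks. Its next sentence ties discontinuation to sections 4.6 and 5.3, and both open by framing their subject as adverse events. Recovery and mask intolerance belong to the description of the treatment period and appear in neither list. That narrower reading is reasonable, and it limits the certain part of the point to the two discretion items. It does not remove those items.

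A reader might go further and infer that the rule makes a real benefit of iNO look like harm. The documents do not support that as a general statement. It requires both that recovery stops are counted and that they are more frequent on iNO. No stopping rates are given, equal stopping yields no false difference, and moderate imbalances give borderline results.

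A reader might also take the temporary stops to be mostly malaria in disguise, since section 8 expects that "the majority of events are likely due to the clinical course of malaria and not to study medications". That remark concerns adverse events in general. Several temporary criteria are qualified as unexplained or persistent, so it cannot be carried over to them directly.

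Two further replies stand in part. Over-inclusive capture is defensible for safety monitoring, and Table 3 shows that a placebo arm normally has event rates of its own; but capturing every stop does not require calling each one a reaction. The recorded reasons do allow the count to be taken apart later; but the rule as written does not ask for that. Finally, section 9.1 specifies no test of reaction rates, so the power figures above only gauge how visible a difference would be.

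**Conclusion.** The rule is wrong as written, at moderate to minor weight. Counting stops at guardian or investigator discretion as adverse drug reactions contradicts the definition in the same section. Whether stops on recovery or mask intolerance are counted is left unclear, and the text should settle it.

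The consequence to expect is inflation in both arms and dilution of any real toxicity difference. Its size depends on stopping rates that the protocol does not give. In the illustration, which assumes independence, a true ratio of 3.0 falls to 1.62 with 10% unrelated stops per arm and to 1.14 with 40%. A spurious excess on iNO is possible only under the two conditions named above.

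The primary endpoint is untouched, and the halting rules in sections 4.6 and 8.2 rest on mortality, so neither is affected.

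**What to change.** Replace the sentence in section 8.1 so that:

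1. All temporary and permanent stops of study gas are tabulated by arm and recorded reason: adverse event, recovery, mask intolerance, guardian choice, investigator discretion.
2. A stop enters the adverse drug reaction count only when its recorded reason is an adverse event. The count is shown twice: for all such stops, and for those judged possibly or probably related to study gas.

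Showing both counts matters. Events in severe malaria can resemble toxicity, and a count filtered only by bedside causality judgement could lose real reactions.

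The cost is one sentence and slightly more tabulation. Section 4.9 already collects the reason for each stop and the causality assessment of adverse events, so no new data are needed. The change concerns counting and reporting only; no rule on when gas is stopped is altered.
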